## Abstract

**Background:**

Relapse in schizophrenia is a major cause of distress and disability and is predicted by changes in symptoms such as anxiety, depression, and suspiciousness (early warning signs [EWSs]). These can be used as the basis for timely interventions to prevent relapse. However, there is considerable uncertainty regarding the implementation of EWS interventions.

**Objective:**

This study was designed to establish the feasibility of conducting a definitive cluster randomized controlled trial comparing Early signs Monitoring to Prevent relapse in psychosis and prOmote Well-being, Engagement, and Recovery (EMPOWER) against treatment as usual (TAU). Our primary outcomes are establishing parameters of feasibility, acceptability, usability, safety, and outcome signals of a digital health intervention as an adjunct to usual care that is deliverable in the UK National Health Service and Australian community mental health service (CMHS) settings. We will assess the feasibility of candidate primary outcomes, candidate secondary outcomes, and candidate mechanisms for a definitive trial.

**Methods:**

We will randomize CMHSs to EMPOWER or TAU. We aim to recruit up to 120 service user participants from 8 CMHSs and follow them for 12 months. Eligible service users will (1) be aged 16 years and above, (2) be in contact with local CMHSs, (3) have either been admitted to a psychiatric inpatient service or received crisis intervention at least once in the previous 2 years for a relapse, and (4) have an International Classification of Diseases-10 diagnosis of a schizophrenia-related disorder. Service users will also be invited to nominate a carer to participate. We will identify the feasibility of the main trial in terms of recruitment and retention to the study and the acceptability, usability, safety, and outcome signals of the EMPOWER intervention. EMPOWER is a mobile phone app that enables the monitoring of well-being and possible EWSs of relapse on a daily basis. An algorithm calculates changes in well-being based on participants’ own baseline to enable tailoring of well-being messaging and clinical triage of possible EWSs. Use of the app is blended with ongoing peer support.

**Results:**

Recruitment to the trial began September 2018, and follow-up of participants was completed in July 2019. Data collection is continuing. The database was locked in July 2019, followed by analysis and disclosing of group allocation.

**Conclusions:**

The knowledge gained from the study will inform the design of a definitive trial including finalizing the delivery of our digital health intervention, sample size estimation, methods to ensure successful identification, consent, randomization, and follow-up of participants, and the primary and secondary outcomes. The trial will also inform the final health economic model to be applied in the main trial.

**Trial Registration:**

International Standard Randomized Controlled Trial Number (ISRCTN): 99559262; http://isrctn.com/ISRCTN99559262

**International Registered Report Identifier (IRRID):**

DERR1-10.2196/15058

## Introduction

### Background

Relapse influences the long-term course of psychosis with rates identified as 28% (range 12%-47%), 43% (range 35%-54%), 54% (range 40%-63%) at 1, 1.5, 2, and 3 years follow-up, respectively [1], and more recent evidence shows similar relapse rates [2,3]. Relapse is also associated with poorer response to subsequent antipsychotic treatment [4]. Relapses can occur in up to 80% of participants at the 10-year follow-up [5] and can lead to higher inpatient and outpatient costs [6].

One important predictor of relapse is lack of acceptance of treatment and unplanned discontinuation of antipsychotic medication [1]. Poorer adherence often signals a lack of engagement with services and failure of services to build a collaborative working alliance [7]. Nonadherence to antipsychotic treatment is predicted by poorer insight, previous experience of involuntary treatment, poorer premorbid functioning, comorbid substance misuse, forensic history, poor relationship with the prescriber, greater deprivation, and transfer to secondary care [8-10]. Relapse itself is an important marker of the severity and complexity of illness and is predicted by previous suicide attempts [11]; depression, hostility, and embarrassment [12]; poorer premorbid functioning; family criticism; substance misuse; social isolation [1]; and negative interpersonal style (possibly linked to poorer utilization of social support) [13].

Birchwood et al [14] pioneered the development of systematic early signs monitoring for relapse and its integration into routine care. It is now known that relapse is the culmination of a process of changes that commence days and sometimes weeks before psychosis symptoms reemerge or are exacerbated. These early warning signs (EWSs) include affective changes and incipient psychosis. These EWSs can be detected as early as 8 weeks before rehospitalization [15]. A systematic review [16] found that the sensitivity of early signs to relapse (proportion of relapses correctly predicted) ranged from 10% to 80% (median 61%) and specificity (proportion of nonrelapses correctly identified) ranged from 38% to 100% (median 81%). Detection of relapse was improved by more frequent monitoring (at least fortnightly) and by the inclusion of both psychotic and affective symptoms.

A significant barrier to relapse prevention is fear of help seeking arising from previous experiences of relapse [17]. For example, people may avoid calling their care coordinator in the context of an increase in EWSs for fear of being admitted to the hospital. Research has demonstrated that fear of relapse is linked to more traumatic experiences of psychosis and hospital admission and greater fear of symptoms, such as voices and paranoia [18]. In a randomized controlled trial (RCT) of relapse detection, fear of relapse contributed independently to the prediction of relapse (sensitivity=72%, 95% CI 52-86; specificity=46%, 95% CI 32-60) compared with EWSs (sensitivity=79%, 95% CI 62-89; specificity=35%, 95% CI 23-50). Fear of recurrence was also associated with greater depression, feelings of entrapment, self-blame, and shame [19]. Therefore, it is important to include fear of recurrence in the monitoring of EWSs.

Fear of illness and stigma are closely related to emotional distress [20] and to poorer insight into schizophrenia [8]. Feelings of fear, depression, and helplessness are common emotional experiences before full relapse [21]. In an effort to minimize the stigma of illness and prevent relapse, people can adopt avoidant coping styles that are associated with increased risk of relapse [20]. These coping styles are associated with greater insecurity in relationships, lower self-esteem, lower levels of adherence, and reluctance to seek help in a crisis. Reluctance to seek help may result from greater fear of relapse arising from experiences of involuntary admission. In this sense, avoidance of help seeking can be understood from the perspective that people with experience of psychosis are attempting to minimize or avert the adverse consequences of help seeking based on their lived experience. A recent systematic review [22] found that greater difficulties in forming relationships were associated with poorer engagement with services, more problematic relationships with staff, and more frequent and longer hospital admissions. In sum, the detection of and action following EWSs may be constrained by poor relationships between service providers and people using services, avoidance of help seeking, perceived stigma, fear of relapse, and reluctance to disclose EWSs.

A Cochrane review focused on the effectiveness of interventions targeting recognition and management of EWSs of relapse in schizophrenia [23]. Significant effects in favor of EWS interventions were found for the number of participants relapsing (15 RCTs; n=1502; risk ratio [RR] 0.53, 95% CI 0.36-0.79) and the number of participants being rehospitalized (15 RCTs; n=1457; RR 0.48, 95% CI 0.35-0.66); however, the methodological quality of the trials was poor in terms of randomization, concealment, and blindness. Future EWS interventions need to address these methodological problems that limit their generalizability to usual care. Until this happens, EWS interventions cannot be recommended for routine implementation in health services [23].

An important aspect of service provision for those people at greatest risk of relapse is having access to an integrated mental health care system that enables clear shared planning for managing risk and relapse prevention. One example of this is the role of joint crisis plans (JCPs) in the United Kingdom. The CRIMSON study [24] was an individual-level RCT that compared the effectiveness of JCPs with treatment as usual (TAU) for people with a diagnosis of schizophrenia. There was no significant impact on the primary outcome (reduced coercion into hospital). It was noted that when faced with crisis, in spite of the considerable effort in developing the JCP with service users, the teams reverted to *custom and practice*. The staff did not consult JCPs in planning the team response to a crisis. Furthermore, people in receipt of services experienced an inability to influence clinicians’ behaviors, and this was interpreted as signaling a lack of respect for their views and opinions. Consequently, they described their interactions with clinicians as *playing the game*, that is, appearing to comply with treatment decisions. Clinicians themselves experienced their interactions with people using services as ritualized, especially in the context of responding to increased risk [25].

Gumley and Park [17] highlighted that relapse prevention based on EWS monitoring relies on the person receiving services initiating help seeking in the context of feeling vulnerable and threatened. Many individuals find help seeking a challenge and may have had difficult or traumatic experiences of psychosis. Delay in help seeking narrows the window of opportunity for successful relapse prevention, which in turn increases reliance on coercive measures confirming pre-existing negative expectations. It is therefore essential to develop and evaluate an intervention that can facilitate safe and honest disclosure of possible EWSs while also reorienting the response of mental health teams and the actions of their staff in a crisis toward a more collaborative approach.

Our conceptual framework for improving relapse detection and prevention aims to understand how EWSs unfold in the context of important caring relationships. Figure 1 provides an illustration of our cognitive interpersonal model for EWSs. Fear of recurrence drives feelings of fear, anxiety, and shame. Coping strategies to regulate emotional distress (eg, increased hypervigilance, worrying, and avoidance) shape care providers’ own cognitive and emotional responses to perceived increased risk of relapse. For example, care providers may interpret increased emotional distress or avoidance (eg, cancelling appointments) as evidence of increased risk prompting changes in clinical care and risk management. These changes may further confirm individuals’ negative expectations of services and fear of recurrence. Therefore, interventions that can enhance positive emotional awareness (through self-monitoring), choice and autonomy (through self-management promotion), and improved communication (through increased understanding) could provide a means to disrupt and change negative interpersonal cycles.

**Figure 1 figure1:**
[figure not shown]
Cognitive interpersonal framework for early warning signs.

Digital technology has the potential to offer a step change that can influence early signs monitoring both for people receiving and providing mental health services [26,27]. Mobile phones to support health care are promising for the delivery of interventions that are unconstrained by the limitations of existing treatment settings. Mobile phones are widely available and are continuously dropping in cost, and nearly 3 billion people are projected to own a mobile phone by 2020 [28]. Mobile phone ownership among people who experience psychosis is increasing with estimated rates of ownership from 66.4% (95% CI 54.1%-77.6%) rising to 81.4% (n=454) in more recent studies [29]. Furthermore, people with psychosis express an interest in the use of mobile phones to enhance contact with services and to support self-management [29,30]. Mobile phones, particularly *mobile phones*, offer opportunities for ecological momentary assessment (EMA) to collect data on repeated occasions, in real time, and in the context of daily life [31]. This enhances the ability to assess individuals in their usual context, temporally close to relevant events, and intensively and repeatedly as psychological processes unfold over time [32]. Bell et al [33] found that across 9 interventions (n=459), interventions for people with psychosis using EMA show satisfactory levels of feasibility and acceptability as well as preliminary evidence of improved clinical outcomes. Furthermore, studies that prospectively assess symptom course using mobile phone apps in people with psychosis show promise [34-45] in terms of feasibility of, acceptability of, and adherence to regular daily monitoring and also delivery of in-time interventions to support coping [36] or delivery of cognitive behavioral therapy [38].

However, studies employing mobile phones to promote relapse detection and intervention are not without their challenges. The Information Technology–Aided Relapse Prevention Program in Schizophrenia (ITAREPS) utilized a weekly text-based monitoring system to detect EWSs in people with psychosis. This system gathers data on early signs of psychosis using text messaging with clinicians notified by alerts where scores breach a specified threshold. Treating clinicians are expected to increase medication by 20% within 24 hours of an alert. In the initial studies [46,47], adherence by people using services and family members was problematic, in that only 47% were described as *high* users with 70% return rates. In the ITAREPS RCT [48], trial adherence improved; however, adherence to the treatment protocol was problematic at 39% largely owing to conflicts between protocol-indicated medication increases and psychiatrists’ clinical judgment. Komatsu et al [49] found that adherence to the ITAREPS protocol was improved when mental health nurses were involved in triaging EWS assessments. More recently, Eisner et al [50] demonstrated that over 6 months, adherence to mobile phone-based assessments of EWSs was 65% and successfully predicted increased psychotic symptoms 3 weeks later.

In sum, mobile phone technology offers a significant opportunity to deliver EMA-based monitoring of changes in well-being that are ecologically valid and contextually sensitive. Preliminary studies show encouraging levels of user acceptability and engagement, and thus, they offer the potential to recognize EWSs and activate timely assessment and intervention to promote self-management and relapse prevention. However, there are important implementation challenges to ensure that these technologies can enhance relationships and shared decision making, particularly during times of increased stress and crisis.

### Objectives

The overall aim of this study is to establish the feasibility of conducting a definitive cluster randomized controlled trial (cRCT) comparing Early signs Monitoring to Prevent relapse in psychosis and prOmote Well-being, Engagement, and Recovery (EMPOWER) against TAU. We will establish the parameters of the feasibility, acceptability, usability, safety, and outcome signals of an intervention as an adjunct to usual care that is easily deliverable in the National Health Service (NHS) and Australian community mental health service (CMHS) settings. The EMPOWER intervention aims (1) to enhance the recognition of EWSs by people using services and their carers and (2) to provide a stepped-care pathway that is either self-activated or in liaison with a carer and/or community health care professional, which then (3) triggers a relapse prevention strategy that can be stepped up to a whole team response to reduce the likelihood of a psychotic relapse.

Specifically, we aim to do the following:

Enhance and tailor our mobile phone software app to deliver EWS monitoring, self-management interventions, and access to a relapse prevention pathway that is firmly embedded in whole team protocols and action.Determine rates of eligibility, consent, and recruitment of potentially eligible participants (people using services, carers, and care coordinators) to the study.
Assess the performance and safety of the EMPOWER Class 1 Medical Device (CI/2017/0039).
Assess the feasibility, acceptability, and usability of the intervention including feedback on suggested enhancements from people receiving the intervention, peer support workers, and clinicians.Assess primary and secondary outcomes to determine preliminary signals of efficacy of the EMPOWER Relapse Prevention Intervention as a basis for the estimation of sample size requirements of a future definitive trial.Undertake a qualitative analysis of relapses to refine the intervention in the main trial.Establish the study parameters and data-gathering frameworks required for a coordinated health economic evaluation of a full trial across the United Kingdom and Australia.

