## Methods

### Trial Design

We will evaluate EMPOWER using a multicenter, 2-arm, parallel group cRCT involving 8 purposively selected CMHSs (2 in Melbourne, Australia, and 6 in Glasgow, Scotland) with 12-month follow-up. The CMHS will be the unit of randomization (the cluster), with the intervention delivered by the teams to people using services and with outcomes assessed within these clusters. The Standard Protocol Items: Recommendations for Interventional Trials checklist is provided as an additional file. The study is planned and implemented in concordance with the Consolidated Standards of Reporting Trials (CONSORT) cluster trial extension [51] and the extension to randomized pilot and feasibility trials [52]. We chose a cluster design as the EMPOWER intervention aims to enable a team-based response to people in receipt of services whose real-time EWS monitoring has activated a relapse prevention pathway. Our CONSORT diagram is detailed in Figure 2.

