### Recruitment and Randomization

The unit of randomization is the CMHS (the cluster). Participating CMHSs will be randomized within stratified pairs to the EMPOWER Relapse Prevention Intervention or to continue their usual approach to care. A statistician at the Centre for Healthcare Randomised Trials (CHaRT) at the University of Aberdeen will provide the allocation codes. The 2 clusters in Australia form a single stratum. The 6 clusters in Glasgow will be paired based on similarity of catchment area in terms of social deprivation or CMHS type (eg, early intervention service).

Researchers will approach each eligible care coordinator and seek their consent to participate in the trial. Before randomization, consenting care coordinators will provide an anonymized list of their current potentially eligible caseload of people using services. This list will then be randomly ordered by CHaRT. Researchers will then approach identified people sequentially in blocks of up to 5 potentially eligible participants and seek informed consent to participate in the study. If there are further participants eligible for inclusion at the end of this block, the researcher will move onto the next block of 5 (if applicable). Care coordinators will provide participants with an easy-to-read information leaflet about the study to enable potential participants to express interest in finding out more information. In Australia, information posters will be displayed within staff areas of participating sites to inform care coordinators of the study and provide contact details of RAs, should they wish to participate.

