We aim to approach and consent on an average of 3 participants per care coordinator (giving a total of up to 120 potential participants). Following consultation with the independent Data Management and Ethics Committee (DMEC) and the Study Steering Committee (SSC) in May 2018, these recruitment objectives were amended to 86 participants. This was because of a number of challenges to recruitment including (1) temporary suspension of the study to apply for registration with the MHRA, which delayed start up to recruitment, (2) comprehensive and detailed screening of all potential trial participants, (3) delays arising from care coordinators approaching potential participants, and (4) high rates of turnover among care coordinators. Following independent methodological and statistical advice, there was clear guidance that the original feasibility aims will be met by the trial, and this change to recruitment targets was approved by the funders. After completing baseline assessments on all consenting service users in care coordinators’ and CMHSs’ caseload, the Clinical Trials Unit (CTU) at CHaRT will conduct randomization of the CMHSs. For Australia, with just 2 clusters, this will be by simple randomization by the CTU. For Glasgow, with 6 clusters, the CTU will create 3 pairs of teams based on similarity of the catchment area in terms of social deprivation (Carstairs) score or CMHS type (eg, early intervention service). The CTU will randomly allocate one member of the pair to the intervention, and the remaining member will be allocated to control.

We will explore in this pilot phase the best method of randomly allocating the clusters in the full trial, specifically to establish what matching factors (if any, and/or if matching at all is appropriate, methodologically) are suitable. Any violations of the study protocol will be recorded and reported to the Research Ethics Committee, SSC, and the independent DMEC.

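### The objectives make the pilot's efficacy signal a basis for sizing the definitive trial, but about 86 participants in 8 teams estimate the effect too imprecisely for that

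*Protocol article*

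**What the plan says.** The Objectives section of the protocol article lists, among the specific aims, an assessment of outcomes whose stated purpose is to "determine preliminary signals of efficacy of the EMPOWER Relapse Prevention Intervention as a basis for the estimation of sample size requirements" for the later definitive trial.

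The Sample Size section justifies the pilot differently. It makes no formal calculation and regards up to 120 service users in 8 teams as enough to establish feasibility and obtain parameters, among them the ICCs. Recruitment and Randomization then lowers the target to 86 and reports advice that the feasibility aims would still be met. The design is a cluster trial "involving 8 purposively selected CMHSs (2 in Melbourne, Australia, and 6 in Glasgow, Scotland) with 12-month follow-up".

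The Background cites a Cochrane review of early-warning-sign interventions, which found for relapse "risk ratio [RR] 0.53, 95% CI 0.36-0.79". The article does not say that this, or any other external source, will set the target difference for the definitive trial. Nor does it caution against using the pilot's own effect.

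**The concern.** A pilot can reasonably inform the nuisance quantities in a sample size calculation: control event rate, standard deviations, ICC, retention and cluster size. The target difference is another matter. It should be the smallest difference worth detecting, and a small pilot estimates the true effect with great error.

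Required sample size varies roughly with the inverse square of the assumed difference, so error in the effect is magnified in the size. If the objective were followed as written, a pilot with a chance large effect would lead to an underpowered main trial. One with a chance small effect would lead to a needlessly large trial, or to one that looks infeasible.

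**Working it through.** **The plan's own figure.** 40 care coordinators × 3 participants = 120. This is recruitment arithmetic; no power, effect size or ICC lies behind it. The amended 86 gives 43 per arm and 86/8 = 10.75 per team, taking equal arms and teams.

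**Inputs**
- Control relapse 28%, range 12% to 47% (Background). The sentence lists three rates against four time points, so reading 28% as the 1-year rate is an assumption.
- True risk ratio (RR) 0.53 (Background), giving 0.53 × 0.28 = 0.1484 in the intervention arm, or about 12 against 6 relapsers.
- ICC 0 and 0.05. The article gives no value; these are assumptions.
- No dropout, which is favourable to the plan.

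**Precision of the risk ratio**
- Variance of log RR = 0.72/(43 × 0.28) + 0.8516/(43 × 0.1484) = 0.0598 + 0.1335 = 0.1933, so SE = 0.440.
- Design effect at ICC 0.05 = 1 + 9.75 × 0.05 = 1.4875, so SE = √(0.1933 × 1.4875) = 0.536.
- 95% CI = exp(ln 0.53 ± 1.96 × SE): **0.22 to 1.25** at ICC 0 and **0.19 to 1.52** at ICC 0.05.
- With a t critical value on 3 df (four pairs minus one), these widen to 0.13 to 2.15 and 0.10 to 2.92.
- At 120 participants (normal critical value) they are 0.26 to 1.10 and 0.20 to 1.37.

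**Chance of the wrong direction**
- Risk difference = 0.28 − 0.1484 = 0.1316.
- SE = √[(0.28 × 0.72 + 0.1484 × 0.8516)/43] = 0.0873 at ICC 0; × √1.4875 = 0.1065 at ICC 0.05.
- P(estimate ≤ 0) = Φ(−0.1316/0.0873) = 0.066 and Φ(−0.1316/0.1065) = 0.108, so **about 7% to 11%**.

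**Chance of halving the main trial, computed two ways**
- Size proportional to 1/difference², variance held constant: the size is halved when the estimate exceeds √2 × 0.1316 = 0.1861. The probability is 1 − Φ(0.0545/0.0873) = 0.27 at ICC 0 and 1 − Φ(0.0545/0.1065) = 0.30 at ICC 0.05.
- Control rate fixed at 28%, variance recomputed: the size is halved at RR of about 0.37. The probability is Φ[(ln 0.37 − ln 0.53)/SE] = 0.21 at ICC 0 and 0.25 at ICC 0.05.
- Together: **roughly 20% to 30%**.

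**Spread of the implied size** (two-sided 5%, 80% power, control 28%, before any design effect). The true requirement is 304 participants. The middle half of pilot estimates runs from RR 0.39 to 0.71 at ICC 0, implying 170 to 884. At ICC 0.05 it runs from 0.37 to 0.76, implying 154 to 1,300.

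**Sensitivity to the control rate**
- At 47%: CI 0.29 to 0.97 (ICC 0) and 0.25 to 1.11 (ICC 0.05). About 1% to 5% of pilots point the wrong way, taking the risk-difference and log-RR scales together.
- At 12%, ICC 0: CI 0.13 to 2.16.

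**Other quantities.** For a continuous outcome at 86 participants the 95% half-width is 0.42 SD (ICC 0) to 0.52 SD (ICC 0.05) with a normal critical value. The ICC is poorly estimated too: its standard error is about 0.07 when the true value is 0.05.

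**The case against.** The objective calls the signals a basis, not the only one, and does not say that the observed difference will become the target difference. The Sample Size section points to ICCs and other parameters, which is legitimate, and assessing outcomes also yields control rates and SDs. This stands in part: sizing from the observed effect is one reading, not a declared procedure. But the sentence ties the efficacy signal itself to sample size, and nothing else in the article supplies a target difference.

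The figures rest on assumed inputs. Eligibility requires a relapse in the previous 2 years, so control relapse above 28% is plausible, and the imprecision is then smaller. That also stands, and is why ranges are given. Even at 47%, the upper limit stays at or below 1 only with an ICC of about 0.01 or less and a normal critical value.

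Stronger readings are tempting, but the article does not support them:
- *That the paired design defeats the efficacy analysis.* Teams are allocated in four pairs ("The 2 clusters in Australia form a single stratum", and in Glasgow "the CTU will create 3 pairs of teams based on similarity of the catchment area"). There are 2⁴ = 16 allocations, so a two-sided randomisation p-value cannot fall below 2/16 = 0.125. But Statistical Analysis plans mixed models and names no randomisation test or significance threshold. The figure shows how little information four pairs carry; it is no error in a planned test.
- *That a chance result would decide whether the main trial goes ahead, or that efficacy will be claimed.* The article states no progression rule based on the effect and makes no such claim.
- *That the abstract's Conclusions repeat the fault.* They say only that "The knowledge gained from the study will inform the design of a definitive trial including finalizing the delivery of our digital health intervention, sample size" and other design matters; efficacy is not mentioned, and this is ordinary pilot wording.

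Recruitment and follow-up are over and the database is locked, so no conduct can change. The definitive trial is still to be designed, however: the section on the usual-care control refers to a main trial application yet to be submitted.

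**Conclusion.** The point holds as a fault in one stated objective. Nothing is wrong with a planned analysis, or with using the pilot to learn relapse rates, ICCs and retention. With 28% control relapse, a true risk ratio of 0.53, 43 per arm, no dropout and an ICC of 0 to 0.05, the interval for the effect runs from a large benefit to harm. Sizing on the estimate would then often give a main trial far too small or far too large. The conclusion does not depend on the assumed ICC, since the interval already spans 1 at ICC 0, and at 28% it would do so even with 120 participants. It weakens towards 47% control relapse and strengthens towards 12%. It is worth correcting because the sizing decision is still to come.

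**What to change.** Reword the objective so that primary and secondary outcomes are summarised by arm with confidence intervals, and so that the pilot informs the definitive sample size only through control relapse rate, SDs, ICC (with its uncertainty), retention and cluster size. State that the target difference will be a minimum important difference agreed in advance and checked against the external evidence cited in the Background, and that the observed pilot effect will not serve as the planning difference.

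The cost is the wording of one objective, carried into the report and the main trial application. No data collection or analysis changes.
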